## Evaluation of implementation processes

Implementation processes (process evaluation) will be explored by assessing barriers and facilitators of a successful implementation, according to the RE-AIM Modell [31], Consolidated Framework for Implementation Science (CFIR) [32] and sustainability frameworks [33].

The purpose is to gain an overview of current practices (status quo) in the centres regarding physical activity interventions in cancer care, and to collect factors associated with these practices as well as the organisational context that may influence the quality of the implementation process. The evaluation additionally focusses on developing and extending the care pathway in the participating centres (CCCs and remote cancer centres).

The assessment of the extent of the implementation (adoption), sustainable implementation (maintenance) and reach follow the RE-AIM framework [31]. Maintenance as the implementation success is based on sustainability of implementation into routine care and its structures and processes in the CCCs. In addition, quality assurance will be evaluated on the basis of quality dimensions (structure, process and outcome quality). Quality assurance includes the use of the care pathway by patients (reach) and utilization.

Barriers, facilitators and suggestions for sustainability will be assessed in a longitudinal questionnaire and interview study conducted with healthcare providers and key informants at seven CCCs in three large regions in Germany (phases 1 and 2) and remote cancer centres (phase 3).

### Participants and recruitment

Key informants and healthcare providers will be surveyed in phases 2 and 3 to record potential changes during the implementation process and outreach. Key informants are defined as individuals with the comprehensive knowledge within their organisation. Healthcare providers include doctors and nurses, nutritionists, psycho-oncologists and social services.

As key informants, the leaders of the physical activity unit within their respective organisations (*n* = 7) are recruited. They will be invited to fill out a postal survey, followed by in-depth semi-structured interviews. The survey will be followed up with two reminders and in-depth semi-structured interviews will be conducted using the survey responses as a basis for the interviews. Key informants will be invited in all three phases to fill out a postal questionnaire followed by an interview. Phases 1 and 2 concentrate on CCCs key informants. The outreach in phase 3 into remote cancer centres will include further key informants. Potential remote centres are ambulatory care oncologists who will receive an incentive for participation.

In addition, each key informant will be requested to enlist at least three healthcare providers who work in the physical activity context for further surveys and interviews. Healthcare providers fulfilling the following criteria are eligible to participate:are at least 18 years old,have been in their current position for at least six months,work directly with patients, andpossess a direct understanding of relevant care procedures, such as existing exercise therapy programmes and care pathways.

To ensure a comprehensive evaluation of all professionals involved into the implementation process, additional interviews with healthcare providers will be conducted in phase 1. In phases 2 and 3 survey and interviews will be conducted. The interviews will take place face-to-face at the CCCs or online according to preferences of the interviewees.

All patients enrolled in the MOVE-ONKO care pathway in phase 2 who filled in both baseline (t0) and 4-week follow-up (t1) questionnaires are eligible for participating in a patient interview. A purposeful sample will receive an invitation to an interview within 2 weeks of returning the t1 questionnaire. Interviews will take place online, via telephone or face-to-face at a place designated by the patient according to preferences of the interviewees.

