Reach [31] comprises the availability of the care pathway for patients and the knowledge gain for participating healthcare providers. Availability will be described by assessing gross and net number of eligible patients and the number of actual patients included. The gross number are all eligible patients who are potential users of the care pathway, i.e. all cancer patients in the participating centres under acute treatment who are at least 18 years old. This number can be estimated from the yearly structured quality reports of each centre. The net number are all patients who can potentially be included given the resource constraints in the centres. There is a limited number of EOGs at the centres recruiting patients for the MOVE-ONKO care pathway. The maximum number of potential patients to be included by the MOVE-ONKO financed staff is derived from combining staff hours and estimated time for recruitment and physical activity counselling. Recruiting staff will document the number of patients approached for recruitment. Gross and net numbers will be compared with the number of actual recruitments taking patients’ willingness to participate into account. In the survey and interviews of key informants and healthcare providers knowledge gain will be measured by the spread of knowledge about exercise therapy in oncology supportive care in CCCs and remote cancer centres.

Qualitative interviews: Two separated interview guidelines are developed for key informants and healthcare provides based on theme complexes of a previous study [18] and on the CFIR framework [32]. Interview guides and questionnaires for key informants and healthcare providers will be further developed during the data collection process and results of previous phases. Interviews will take place at CCCs, remote centres or online. Both questionnaires and interview guides are pretested for comprehension and applicability.

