### Sample size calculation

Since no effects are analysed for the implementation outcomes, no sample size calculation is was made. The case number planning of the key informants and healthcare providers is determined by the project structure. The sampling of the key informants and healthcare providers is limited by the number of the seven cooperating CCCs and the associated 49 remote centres. All key informants will be included into the quantitative survey (phase 1/2: *n* = 7, phase 3: *n* = 56). Interviews will be conducted with CCCs key informants (*n* = 7) in all phases and in phase 3 with additional 14 key informants of the remote cancer centres. Purposeful sampling will be used for selection.

In phases 2 and 3, 105 healthcare providers will be recruited for the questionnaire survey in the CCCs. It will be assumed that each CCC (*n* = 7) has at least 15 healthcare providers involved into the care structures. In phase 3, healthcare providers in remote cancer centres will also be included in the survey. Based on the assumption that each CCC will reach additional seven remote cancer centres in phase 3 with five healthcare providers available for survey, a further 245 healthcare providers will be surveyed (total in phase 3: *n* = 350).

Purposeful sampling is used to conduct in-depth interviews with at least 18 healthcare providers in all phases.

For the qualitative interviews of patients, at least five patients at all CCCs and at least ten patients at remote cancer centres are recruited by purposeful sampling until saturation is reached. Sampling is informed by sex, age, tumour entity, exercise therapy, and experiences with the MOVE-ONKO care pathway as reported in patient questionnaires which are part of the evaluation of intervention outcomes.

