As independent cohorts of healthcare providers will be surveyed and interviewed, no within-person comparisons can be made. Key informant recruitment of healthcare providers may lead to social desirability bias. Outreach in phase 3 is hypothetical and it remains uncertain whether each CCC will reach an additional 7 remote cancer centres.

In the final phase of the study, the results will be published as a report. The results will be made available to the scientific community in the form of scientific publications and conference papers. Aggregated results of each CCCs implementation success will be made available to participating centres on request.

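### The provider survey is meant to show change and the spread of knowledge, but it does not link likely repeat respondents in the seven CCCs and admits only staff who already know the local exercise programmes

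*Protocol article*

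**What the plan says.** All references are to the protocol article.

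- **Purpose: change.** Participants and recruitment (implementation): "Key informants and healthcare providers will be surveyed in phases 2 and 3 to record potential changes".
- **Purpose: knowledge.** Measures (implementation), paragraph on Reach: "knowledge gain will be measured by the spread of knowledge about exercise therapy in oncology supportive care", in the CCCs and remote centres. In Table 2, the physical activity competence, knowledge and attitude measure for providers (PAHCO) is collected in phases 2 and 3 only.
- **Recruitment.** Participants and recruitment (implementation): "each key informant will be requested to enlist at least three healthcare providers who work in the physical activity context". Among other criteria, eligible providers must already have a direct understanding of relevant care procedures, with existing exercise programmes given as an example.
- **Numbers.** Sample size calculation (implementation): "In phases 2 and 3, 105 healthcare providers will be recruited for the questionnaire survey in the CCCs", because each CCC "has at least 15 healthcare providers involved into the care structures". Phase 3 adds five providers from each of 49 remote centres, 350 in all. No formal calculation is made, on the ground that no effects are analysed for implementation outcomes.
- **Linkage.** The Discussion describes independent provider cohorts, so that "no within-person comparisons can be made". It also names social desirability as a possible result of recruitment through key informants.

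**The concern.** Two stated aims do not fit the stated design.

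First, change between phases 2 and 3 is to be recorded, and both waves draw on the same seven CCCs. If some staff answer twice, the waves are not independent. Calling them independent does not make them so, and without a link the correlation that would sharpen the estimate of change is lost. PAHCO has no phase 1 measurement in providers, so the phase 2 to 3 contrast is the main quantitative evidence on provider knowledge.

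Second, the Background gives as a reason for the project that many providers lack the competence to inform patients and do not know what their own organisation offers. The survey excludes people without a direct understanding of local exercise programmes and pathways. It therefore cannot show knowledge reaching the staff in whom the gap is said to lie.

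A lesser matter is that the invitation asks for three or more providers where the plan counts on 15 or five, and the article does not say how one becomes the other.

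**Working it through.** **1. The plan's own figures.** CCC providers: 7 × 15 = 105. Remote providers: 49 × 5 = 245. Phase 3 total: 105 + 245 = 350. All three reproduce.

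**2. What the invitation guarantees.** There are 7 key informants in phase 2 and 56 in phase 3, each asked for at least three providers.

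- Phase 2: 7 × 3 = 21, and 21/105 = 20%.
- Phase 3: 56 × 3 = 168 (21 from CCCs, 147 from remote centres), and 168/350 = 48%.

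These are floors, with no upper limit stated.

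**3. How likely is overlap in the CCCs?** Each wave needs 15 providers per CCC. Two waves with no one in common need 15 + 15 = 30 eligible staff per CCC, or 7 × 30 = 210 in all. The plan assumes at least 15, or 105 in all. With N eligible staff per centre and no turnover, at least 30 − N must answer twice (for N from 15 to 30):

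| N per CCC | Forced repeats, of 15 |
|---|---|
| 15 | 15 |
| 20 | 10 |
| 25 | 5 |
| 30 | 0 |

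At N = 30, random selection in each wave would still give 15 × 15/30 = 7.5 expected repeats, or half. The true N and the turnover are not given, so overlap is an inference.

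**4. Effect on precision.** Take 105 CCC respondents per wave, outcome SD = 1, a fraction f answering twice and within-person correlation r. For the difference of the two wave means:

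SE = √[2(1 − f·r)/105]

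The documents give no r for providers, so r = 0.5 is an assumption.

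| Case | SE (SD units) | Against unlinked |
|---|---|---|
| Analysed as independent | √(2/105) = 0.138 | – |
| f = 0.5, r = 0.5 | √(1.5/105) = 0.120 | 13% smaller |
| f = 1, r = 0.5 | √(1/105) = 0.098 | 29% smaller |
| f = 1, r = 0.3 | √(1.4/105) = 0.115 | 16% smaller |
| f = 1, r = 0.7 | √(0.6/105) = 0.076 | 45% smaller |

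At full overlap and r = 0.5, the 95% half-width falls from 1.96 × 0.138 = 0.27 to 1.96 × 0.098 = 0.19 SD. An unlinked analysis reports 0.138 whatever the overlap, so with positive correlation its SE is too large. Clustering within the seven centres is ignored throughout.

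**5. Knowledge outcome against eligibility.** The Reach paragraph wants the spread of knowledge in the centres. Eligibility admits only people who already understand the existing programmes and pathways. A gain seen in this group is a gain among informed staff. A centre where knowledge spread to previously uninformed staff, and one where it did not, could look the same in this survey.

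**The case against.** The case on the other side is substantial.

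- **The recruitment numbers.** A reader might infer that the survey will yield about 21 and 168 people. The text does not support that: the request is for at least three, with no ceiling, and the targets of 15 and five are stated separately.
- **Linkage is disclosed.** The Discussion says openly that the cohorts are independent and that within-person comparison is not possible. A reader might infer that repeat respondents are part of the plan; the article does not say so. Because at least 15 per CCC is a minimum, full overlap is not implied either. This stands. But disclosure does not show how independence would be secured when the same seven centres are surveyed twice.
- **The longitudinal label** in Evaluation of implementation processes covers key informants as well, and CCC key informants are surveyed in every phase. Repeated surveys of the same centres are longitudinal at centre level, so the label is no contradiction.
- **No effects are analysed.** The sample size section says so, and an SE argument then matters less. Yet the same article sets out to record changes and measure knowledge gain, and Data analysis applies the primary scheme to other quantitative outcomes. If that includes provider outcomes, the scheme needs paired values that the Discussion says will not exist.
- **Mixing of centre types.** Remote staff are 245/350 = 70% of the phase 3 target, so a reader might infer that change will be confounded with centre type. Nothing says that the pooled 350 will be compared with the 105.
- **Ceiling effect.** A reader might infer that knowledge starts near its maximum. No figure supports this, and the criterion concerns care procedures rather than mastery of exercise oncology.
- **Informed respondents are needed** for the NoMAD, training and app items, and the Reach paragraph speaks of gain in participating providers. This is a good reason not to drop the criterion for the whole survey.

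**Conclusion.** The point holds in a limited form. The article assigns the provider survey two tasks, change between phases and spread of knowledge, that its design serves poorly.

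On change, overlap in the CCCs is likely unless each centre has about 30 or more eligible staff or high turnover. Leaving it unlinked costs precision: at r = 0.5, an SE of 0.138 where 0.098 (full overlap, best case) or 0.120 (half overlap) could be had. These figures rest on the assumed r, on 105 completed questionnaires per wave and on ignoring clustering. The error is towards missing a real change. A reader might infer from the word independent that SEs will be too small and findings spurious; with positive within-person correlation the reverse is true.

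On knowledge, the survey can support a statement about informed, participating providers but not about spread across a centre. The disclosed social desirability bias is a different problem and does not cover this.

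The gap between a request for three and targets of 15 and five is a matter of wording to align, not a contradiction. This is a secondary process evaluation; the patient primary outcome is untouched.

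**What to change.** 1. **Link.** Add a self-generated pseudonymous code to the CCC provider questionnaires in phases 2 and 3. If the phase 2 wave has already closed, ask in phase 3 whether the respondent answered before, so that the overlap is at least known.
2. **Analyse.** Estimate phase 2 to 3 change in CCC staff only, with a model that allows for repeat respondents and for centre. Show remote staff separately. State in the Discussion that the CCC waves may overlap.
3. **Knowledge claim.** Either limit it to gain among informed, participating providers, or relax the direct-understanding criterion for the knowledge items only, keeping it for the NoMAD, training and app items.
4. **Invitation.** Reword the request to match 15 per CCC and five per remote centre, with an allowance for non-response. The article gives no response rate. If 50% to 80% reply (assumption), about 19 to 30 invitations per CCC (15/0.8 to 15/0.5) and 6 to 10 per remote centre (5/0.8 to 5/0.5) are needed.

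Cost: one code item, a data-protection check and possibly a small loss of response. Linked comparison works only for items kept unchanged between phases; since the questionnaire is to be adapted as the project proceeds, the items meant to show change, PAHCO above all, should be held fixed. Relaxing eligibility for the knowledge items would also mean reaching a wider group of staff.

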### Measures

Quantitative survey and documentation: A questionnaire is created to survey key informants and healthcare providers based on the CFIR [34] and sustainability frameworks [33]. It includes both established, validated scales and self-developed items. Outcomes and measures are overlapping for both groups and are therefore presented together (Table 2). The questionnaire's development is part of the evaluation process and will be adapted to further phases as an iterative process. The survey will focus on indicators of structural quality, including the structural characteristics of the organisation and its respective units such as size and sponsorship, the exercise therapy unit's resources including staffing and qualifications. To assess process quality, data and information on organisational processes such as standardisation of patient care processes, existing exercise therapy services and existing collaborations and the current care pathway in the CCC will be collected. Moreover, indicators of organisational culture such as social capital [35], organizational change attitudes [36], and organisational health literacy [37] will be measured (Table 2). Socio-demographic information includes sex, age, profession, position within the organisation, job tenure, and professional experience in the relevant field will be collected for healthcare providers and key informants.

**Table 2 Tab2:** Quantitative survey for healthcare providers and key informants

Outcomes	Measures	Data collection time	Participants
Structural characteristics	Self-developed questions on size and sponsorship	Phase 1/2/3	KI
Personal resources	Self-developed questions on qualifications	Phase 1/2/3	KI
Organisational culture	- SOCAPO-E [35] - Change Attitude Scale [36]	Phase 1/2/3	KI
Organisational health literacy	HLHO-10 [37]	Phase 1/2/3	KI
Equipment and Facilities	Self-developed questions on technical and spatial equipment	Phase 1/2/3	KI and HCP
Cooperation and networks	Self-developed questions	Phase 1/2/3	KI and HCP
Work intensity	Self-developed questions	Phase 1/2/3	KI and HCP
Physical activity-related health competences and knowledge and attitudes towards physical activity	PAHCO [23]	Phase 2/3	HCP
Technology commitment	Technology commitment (TB) [38]	Phase 2/3	KI and HCP
Sustainability	NoMAD [39, 40]	Phase 2/3	KI and HCP
Experience with MOVE-ONKO training and App use	Self-developed questions	Phase 2/3	HCP
Adherence	Self-developed questions on perceived motivation of the patients by healthcare providers and utilisation behaviour of the patients	Phase 2/3	HCP

*KI* key informants, *HCP* healthcare providers, *SOCAPO-E* Social capital of healthcare organizations reported by employees, *HLHO-10* health literate health care organization 10 item questionnaire, *PAHCO* physical activity-related health competence, *NoMAD* Normalisation Measure Development questionnaire, *TB* short scale for measuring technology commitment

Adoption [31] will focus on trained healthcare providers and patients. For healthcare providers, the number of trained EOGs and EOSs will be documented. During the study, the number of counselling encounters per trained person will be assessed. Feedback on the training in phase 2 (implementation in CCCs) will be used to give recommendations for implementation in phase 3 (outreach). It will also be monitored how the information platform and APP are used by healthcare providers and patients. APP and platform provide routine data. Sources for routine data in the APP are filled by questionnaires and anamnesis, as well as usage data, usage behaviour, and intervention documentation (therapy goals, training). The following criteria will be observed:number of screenings in CCCs and remote cancer centresnumber of included patients with complete anamneses before recommending an individual exercise therapy based on a shared decision as documented in the patient filenumber of included patients with an individual exercise therapy recommendation as documented in the patient file and reported by patients in questionnairenumber of included patients taking up exercise therapy as documented in the patient file or reported by patients in questionnairedistance between residence and place of therapy for patients taking up exercise therapy as reported by patients in questionnairenumber of patients who train via app or in the recruiting centres and receive support according to the therapy plan as documented in the APP and reported by patients in the questionnairenumber of healthcare providers who interact via APP

Reach [31] comprises the availability of the care pathway for patients and the knowledge gain for participating healthcare providers. Availability will be described by assessing gross and net number of eligible patients and the number of actual patients included. The gross number are all eligible patients who are potential users of the care pathway, i.e. all cancer patients in the participating centres under acute treatment who are at least 18 years old. This number can be estimated from the yearly structured quality reports of each centre. The net number are all patients who can potentially be included given the resource constraints in the centres. There is a limited number of EOGs at the centres recruiting patients for the MOVE-ONKO care pathway. The maximum number of potential patients to be included by the MOVE-ONKO financed staff is derived from combining staff hours and estimated time for recruitment and physical activity counselling. Recruiting staff will document the number of patients approached for recruitment. Gross and net numbers will be compared with the number of actual recruitments taking patients’ willingness to participate into account. In the survey and interviews of key informants and healthcare providers knowledge gain will be measured by the spread of knowledge about exercise therapy in oncology supportive care in CCCs and remote cancer centres.

Qualitative interviews: Two separated interview guidelines are developed for key informants and healthcare provides based on theme complexes of a previous study [18] and on the CFIR framework [32]. Interview guides and questionnaires for key informants and healthcare providers will be further developed during the data collection process and results of previous phases. Interviews will take place at CCCs, remote centres or online. Both questionnaires and interview guides are pretested for comprehension and applicability.

The patient perspective of the implementation process will be evaluated with patient interviews. They will focus on experiences with the components of the care pathway: how they were addressed and informed, their impression of the physical activity counselling and of the information they were given, which recommendations they received, if they followed them and how they experienced the therapy. Additionally, patients will be asked to report on transfers within the pathway, i.e. EOG to EOS, counselling and recommendation to exercise therapy and physical activity, and on difficulties that arose including digital challenges when using the information platform or the MOVE-ONKO APP. Interview guidelines are based on research questions, discussed in the research team and adapted as necessary.

